### Statistical analysis

Data will be described using univariate analysis (distributions, frequencies, and means). The intervention assignment will be examined in relation to HIV-1 plasma and cART adherence. Analyses will be intention-to-treat. As this is a small sample size we will only be able to evaluate parsimonious models to explore effect of the intervention, and not include all mediating and potentially confounding variables. Generalized estimating equations (GEEs) will be used to model adherence rates to account for the multiple measurements of each subject and allow all subjects, regardless of the number of visits, to be included in the analysis. Analyses also will be conducted within-person, comparing baseline to follow-up session responses. As GEEs require strong assumptions regarding missing data (missing completely at random), analyses will be repeated using the subset of subjects with complete data.

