## Methods

### Study aim and design

The MAHILA project is being conducted through a Collaborative Research Partnership between investigators at the National Institute of Mental Health and Neuro Sciences (NIMHANS) and Yale University. The study is designed to evaluate the feasibility, acceptability, fidelity and preliminary efficacy of a standardized mobile phone intervention in a randomized, controlled pilot study in which 120 HIV-infected women are randomized to treatment as usual (TAU) alone or TAU plus the mHealth (delivered over 16 weeks). After baseline assessment, women are randomly assigned to treatment condition in a 1:1 allocation and outcomes (adherence, HIV-1 RNA plasma [viral load], mental health) are evaluated at 4, 12, 24 and 36 weeks post-randomization (see Fig. 1). The primary hypothesis is that TAU plus the mobile phone intervention will be more effective than TAU in improving adherence to cART and clinical outcomes at 24 weeks post-randomization. Other hypotheses are that the mobile phone intervention will be feasible and acceptable to women living with HIV, fidelity of the intervention will be maintained, and the intervention will improve HIV adherence by concurrently addressing prominent barriers (e.g., depressive symptoms) and improving knowledge, support and problem solving for better engagement in care and adherence.

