### Sample size and eligibility criteria

One hundred and twenty participants will be enrolled, with 60 in each treatment arm. This sample size is consistent with developmental research with the primary aim of assessing the feasibility, acceptability and preliminary efficacy of a new behavioral intervention [40]. It is also large enough to allow for a diverse set of participant characteristics representative of the target population.

To be eligible, a woman must be 1) able to give informed consent, 2) able and willing to be contacted by mobile phone, 3) 18 years of age or older, 4) speak Kannada, English or Hindi, 5) HIV+ and taking cART for less than six months, and 6) screen positive for depressive symptoms or psychosocial risk factors. Women are screened for depression with the Centre for Epidemiologic Studies Depression Scale (CES-D) [41] and for psychosocial risk factors with the Psychosocial Vulnerability Checklist (PSVC). The PSVC was developed by the researchers based on a review of studies among women with HIV, especially in LMICs [26, 28, 42, 43]. It consists of 14 items which assess level of financial strain, social support, violence, substance abuse, mental health problems and suicide ideation.

Women are excluded from participation if they have any condition that, in the opinion of the site investigator, would compromise their ability to participate. Women who screen positive for active suicidal ideation are also excluded. All women with > 16 CES-D or active suicidal thoughts are referred for treatment per a standardized, written protocol.

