### Measures

All study assessments (baseline and 4, 12, 24 and 36 weeks post-randomization) are conducted by trained study staff who are blind to treatment allocation. Assessments are typically conducted in person in the Belgaum ART Centre, but there is some allowance for mobile phone-based follow-up assessments in cases where participants are unable to return to the study site. The data from the forms can be exported in different formats, such as Microsoft Excel file format (.xls) for further processing.

*Adherence* is measured with the AIDS Clinical Trails Group (ACTG) Adherence Questionnaire [52]. The questionnaire queries the patient on the number of doses missed of an ART medication during each of the 4 days before a clinic visit (e.g., “How many doses did you miss yesterday, the day before yesterday, 3 days ago, and 4 days ago?”). It has been used widely in the U.S. and India and has shown good validity and reliability [53].

*Plasma HIV-1 RNA* concentration is used as the clinical criterion and primary outcome variable. Plasma HIV RNA concentration is measured in copies per millilitre (Roche Amplicor HIV-1 Monitor Test). The threshold for detectability of HIV viral load 50 copies/mL.

*Depression* is measured with the Centre for Epidemiologic Studies Depression Scale (CES-D) [41, 54]. CES-D (α = 0.88-0.91) is a 20 item screening tool for depressive symptomatology. All items are rated using a 4 point ordinal scale with the responses based on occurrence of symptoms in the past one week.

*Illness representation* is measured with the Brief Illness Perception Questionnaire (IPQ-B), a 9-item questionnaire designed to rapidly assess cognitive and emotional representations of illness [55]. The IPQ-B uses a single-item scale approach to assess perception on a 0–10 response scale, with higher scores representing more threatening illness perceptions. The scale has demonstrated good test-retest reliability (Pearson correlations 0.24-0.73) and moderate to good correlations when tested for concurrent validity (Pearson correlations 0.32–0.63).

*Symptom Distress* is measured with the HIV Symptom Index, a 20-item valid and reliable (α = 0.92) measure of overall HIV symptom frequency and level of bothersomeness [56].

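### The complete-case repeat cannot test the GEE's missing-completely-at-random assumption, because it relies on essentially the same assumption

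*Protocol article*

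**What the plan says.** All statements on analysis are in the protocol article, Statistical analysis section. It says "Analyses will be intention-to-treat". For adherence, "Generalized estimating equations (GEEs) will be used to model adherence rates", partly because this will "allow all subjects, regardless of the number of visits, to be included in the analysis". It then adds: "As GEEs require strong assumptions regarding missing data (missing completely at random), analyses will be repeated using the subset of subjects with complete data". The article describes no other missing-data or sensitivity analysis.

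The design facts that bear on this are elsewhere in the article:

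- Sample size and eligibility criteria: "One hundred and twenty participants will be enrolled, with 60 in each treatment arm".
- Measures: "All study assessments (baseline and 4, 12, 24 and 36 weeks post-randomization) are conducted by trained study staff", and "there is some allowance for mobile phone-based follow-up assessments in cases where participants are unable to return to the study site".
- Study aim and design: the primary hypothesis is that the intervention will be "more effective than TAU in improving adherence to cART and clinical outcomes at 24 weeks post-randomization".

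Attrition is recorded as a feasibility measure, but no expected rate is given.

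**The concern.** The section identifies a real weakness of the GEE and then answers it with an analysis that has the same weakness. Restricting to women with complete data is valid only if, within each arm, the completers are representative of everyone randomised to it. If that holds, the all-available-data GEE was already sound. If it fails, the repeat fails too, and it has also thrown away the visits that partly observed women did contribute.

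The assumption is open to doubt in this trial. Women are enrolled because they have depressive symptoms or psychosocial risk factors that the Background links to poor adherence and poor access to care. Only one arm receives proactive nurse calls, which aim in part at engagement in care. Loss to follow-up could therefore depend on earlier adherence, and differently by arm.

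Two misreadings are then possible. Similar results could be reported as robustness when both are biased the same way. Different results could cast doubt on the less biased of the two.

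**Working it through.** **No figure to reproduce.** The article states no dropout rate, power or effect size, so every rate below is an assumption.

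**Step 1: how many women the repeat would drop.** With four follow-ups and loss d per visit, the expected number of complete records is 120 × (1 − d)^4.

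- d = 3%: 120 × 0.97^4 = 106, so 14 are excluded.
- d = 5%: 120 × 0.95^4 = 98, so 22 are excluded.
- d = 10%: 120 × 0.90^4 = 79, so 41 are excluded.

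The GEE uses whatever visits these women did provide.

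**Step 2: bias under different dropout rules (simulation A).** There were 20,000 women per arm, so the results show bias and little sampling noise. Adherence was binary at five visits, with within-person latent correlation of about 0.4 to 0.6. Week-24 adherence was 70% in control and either 85% or 70% with the intervention. Dropout was permanent, leaving 11% to 32% of an arm incomplete. Complete cases are women observed at all five visits. The per-visit dropout rules were:

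- Completely at random: 6% for everyone.
- Arm only: 9% control, 3% intervention.
- Earlier non-adherence, control only: 25% after a non-adherent visit in control, otherwise 3%.
- Earlier non-adherence, same rule in both arms: 18% after a non-adherent visit, otherwise 2%.
- Opposite by arm: control 22% after a non-adherent visit, otherwise 2%; intervention 8% after an adherent visit, otherwise 2%.
- Current unseen value, control only: 25% in control if the visit about to be missed is non-adherent, otherwise 3%.

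The table shows the week-24 difference, intervention minus control. Full data is the value before any dropout.

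| Dropout rule | True difference | Full data | GEE, independence | GEE, exchangeable | Complete cases |
|---|---|---|---|---|---|
| Completely at random | 0 | 0.008 | 0.008 | 0.008 | 0.008 |
| Arm only | 0 | 0.003 | 0.000 | 0.000 | 0.001 |
| Earlier non-adherence, control | 0 | -0.001 | -0.048 | -0.002 | -0.091 |
| Earlier non-adherence, both | 0 | -0.002 | 0.000 | -0.000 | -0.002 |
| Opposite by arm | 0 | -0.007 | -0.058 | -0.004 | -0.113 |
| Current unseen value, control | 0 | -0.003 | -0.081 | -0.060 | -0.095 |
| Completely at random | 0.150 | 0.142 | 0.143 | 0.143 | 0.142 |
| Arm only | 0.150 | 0.146 | 0.148 | 0.146 | 0.147 |
| Earlier non-adherence, control | 0.150 | 0.151 | 0.105 | 0.146 | 0.060 |
| Earlier non-adherence, both | 0.150 | 0.145 | 0.133 | 0.137 | 0.118 |
| Opposite by arm | 0.150 | 0.152 | 0.106 | 0.157 | 0.053 |
| Current unseen value, control | 0.150 | 0.145 | 0.065 | 0.085 | 0.050 |

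Complete cases were unbiased only where the GEE was too. In every other row they were further from the full-data value than either GEE.

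**Step 3: milder arm contrast (simulation B).** There were 15 runs of 2,000 women per arm, correlation 0.6, adherence about 75% and no true difference. After a non-adherent visit, dropout was 25% in control and 8% in intervention, otherwise 5%. The full-data difference was 0.005. Subtracting it gives the bias:

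- Complete cases: -0.066 − 0.005 = -0.071.
- Available cases: -0.038 − 0.005 = -0.043.
- Exchangeable GEE: -0.009 − 0.005 = -0.014.
- Multiple imputation: 0.006 − 0.005 = 0.001.
- Missing counted as non-adherent: 0.096 − 0.005 = 0.091.

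**Step 4: larger run (simulation C).** This used 400,000 women per arm, B's dropout rates and correlation 0.4 to 0.6. When dropout depended on earlier adherence, the difference was -0.058 to -0.068 for complete cases and -0.025 to -0.037 for available data. When it depended on the unseen current value, the figures were -0.056 to -0.066 and -0.050 to -0.058. In that second case the two analyses nearly agree and both are wrong by 5 to 7 points.

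**The case against.** **The repeat is secondary and the trial is a pilot.** The all-available-data GEE is the main analysis, and the stated aims are feasibility, acceptability, fidelity and preliminary efficacy. At 60 per arm and 75% adherence, the standard error of a difference is √(2 × 0.75 × 0.25 / 60) = 0.079, so a bias of 7 points is below one standard error. This stands, and it limits the severity. It does not make the repeat a test of the assumption it is meant to test.

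**A reader might infer that the plan breaks intention-to-treat.** It does not do so in the main analysis, because the GEE keeps women with any number of visits. The departure is confined to the repeat, set against a sentence that covers all analyses.

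**A reader might infer that completers would override the GEE if the results differ.** The text does not say so. A gap could even signal that the assumption fails. It would still give no better estimate, and the absence of a gap would not support the assumption.

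**The bias depends on the chosen dropout rule.** It does: the table has several rows with none. The protocol also has features that limit or reveal loss. Both arms receive phones, phone assessment can recover self-reported adherence, and attrition and reasons for drop-out are recorded.

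**A reader might infer that HIV-1 RNA will be missing for women followed by phone.** A call cannot yield plasma, but the Measures section does not say when blood is drawn or whether it can be obtained later. The Statistical analysis section assigns the GEE only to adherence. Missing RNA is a possibility, not something the document establishes.

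**Conclusion.** The point holds in limited form. The plan gives a reason for its missing-data check, and the check does not answer that reason. This is a method the article fixes badly, not detail left to an unseen analysis plan.

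The size is conditional. With no true difference and heavier dropout after non-adherence in control, complete cases were biased by about -6 to -9 points at week 24, against about 0 to -5 for the GEE depending on working correlation. The negative sign works against the intervention. The opposite-by-arm rule in simulation A is more extreme, with complete cases at -0.113. There was no bias under missing completely at random, under arm-only dropout, or under the null when both arms followed the same rule. All dropout rates, adherence levels and correlations are assumptions. The document therefore does not support saying that the trial's arm comparison is biased, only that the planned check could not show whether it is.

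This should be fixed before the outcome analysis, but it is not a fatal fault.

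**What to change.** In the Statistical analysis section, replace the stated check on the adherence GEE with the following:

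- An analysis valid under missing at random that includes every randomised woman: multiple imputation by arm using baseline and all earlier visits, or inverse-probability-weighted GEE.
- A delta or tipping-point analysis that varies the missing-data assumption separately in each arm. It is needed because, when dropout depended on the unseen value, both GEEs and the complete-case analysis were biased.
- The complete-case repeat, if kept, labelled as descriptive and not cited as evidence of robustness.

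Apply the same approach to week-24 HIV-1 RNA if values are missing. Counting every missing value as a failure in both arms is not a substitute: it is one single imputation, it does not bound the arm difference, and for adherence in simulation B it had the largest bias (0.091).

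The cost is revised wording and a little extra programming. No new data are needed.

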## Discussion

To our knowledge, the current study is the first clinical trial to examine the effects of a nurse delivered mobile phone based self-care intervention for women with HIV infection who have depression or psychosocial risk factors in a LMIC [32]. Results from this study will inform the development of interventions for achieving improved clinical benefits and recommendations for mHealth service delivery, from the clinic to national and international policy levels. Findings will also contribute to understanding how mobile technology interventions motivate better health and self-care among women with HIV. Furthermore, in addition to outcome data, respondent and provider satisfaction that are collected as part of this study protocol may provide guidance to HIV and mHealth experts who are seeking to evaluate mobile phone programs for HIV prevention, care, and treatment.

The protocol focuses on mHealth impact on psychological behavioral and physical health; assesses implementation issues unique to mHealth interventions; and also looks at the gender intentionality of the intervention, all of which are priorities for evidence generation in the area of mobile phones for health among women in LMICs. The study will also help us in identifying any risks that women might face related to the mobile intervention such as disclosure issues, any increase in stigma or escalation of partner violence.

There are a few study limitations worth noting. Self-reported adherence to cART has notable limitations [62–65]. We have, however, measured HIV-1 RNA in plasma which is the gold standard for monitoring the efficacy of HIV treatment and measuring the validity of adherence reports. If a patient’s virus is known to be sensitive to current therapy, a detectable viral load likely represents poor adherence [66]. The health behavior constructs we are assessing have not often been evaluated in mobile phone interventions, but prior research and focus group data from other projects suggests that the proposed constructs are affected by mHealth programs [29, 67, 68]. In addition, we will not be able to control external factors that may confound study results, such as medication supplies or health system challenges, weather, civil or political influences, or other health programs occurring in study communities during the intervention period, although we will document these contextual factors to help with interpretation of findings.

The study has several strengths. It is the first trial using a mHealth non text based intervention among women with HIV infection in a LMIC; biases and contamination have been minimised by adequate allocation concealment and by ensuring that the teams of assessors and interventionists are in two different geographical locations. The intervention itself is theory driven and is based on the self-regulatory model of ART adherence [29]. Both groups of women have been given mobile phones to ensure blinding and remove any effect of owning a phone rather than receiving an intervention. Adequate training and supervision is provided to the nurses including a periodic review of call recordings by the investigators to ensure fidelity. Standard operating procedures have been developed for women who report mental health problems, suicidality or domestic violence. Any adverse effects or difficulties related to the intervention will be recorded. Multiple outcomes including adherence, mental health outcomes, quality of life and biological parameters of disease progression (e.g., HIV-1 RNA) are measured. An important outcome that has not been studied in previous trial will include respondent and provider satisfaction with the intervention.

## Conclusions

This nurse led mobile phone intervention for improved self-care among women with HIV infection who have depression and/or psychosocial vulnerabilities will provide important evidence for the usefulness, feasibility and acceptability of this novel intervention. Results of this trial will be important in informing future mHealth interventions for this population and for women with other chronic medical illness in LMICs.

## Abbreviations

ACTG, AIDS clinical trials group; ART centre (antiretroviral centre) - a government-sponsored HIV treatment clinic; cART, combination antiretroviral therapy; CES-D, centre for epidemiologic studies depression scale; CUG, closed user group;.xls - microsoft excel file format; DSMB, data safety and monitoring board; GEEs, generalized estimating equations; HIV, human imuunodeficiency virus; HIV-1 RNA plasma (viral load) - a quantitative measurement of viremia; ICMR, Indian council of medical research; IPQ-B, brief illness perception questionnaire; IRB/ECs, institutional review board or ethics committees; LMICs, low- and middle-income countries; mHealth, mobile health, a term used for the practice of medicine and other health care services supported by mobile devices; MVC (Model-View-Controller), a software architectural pattern mostly (but not exclusively) for implementing user interfaces; MySql, an open-source relational database management system; NIMHANS, national institute of mental health and neuro sciences; PSVC, psychosocial vulnerability checklist; SIM card, subscriber identity module card is a portable memory chip used in cell phones; TAU, treatment as usual; WHOQOL-HIV BREF, world health organization quality of life HIV short measure
